## Abstract

**Background:**

Nutritional support is essential in the care of critically ill children since malnutrition in this population is associated with increased morbidity and mortality. Injury in patients admitted to pediatric intensive care units (PICU) results in a catabolic state and augmented protein breakdown, leading to a negative protein balance. Current recommendations about protein prescription in the PICU are fundamentally based on expert opinions, and the minimum threshold is 1.5 g/kg per day of protein, although protein needs could be higher in certain subgroups of patients. The main objectives of the present study are to examine whether the administration of a protein-enriched infant formula increases the serum levels of total proteins, albumin, prealbumin, transferrin, and retinol and improves nitrogen balance and to analyze the effect of the high-protein diet on energy expenditure. A secondary objective is to register possible secondary effects of the protein-enriched diet.

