**Methods:**

A multicenter prospective randomized controlled trial (RCT) will be performed in three hospitals. Patients meeting inclusion criteria will be randomly allocated to one of three enteral feeding formulae with different protein contents. Blood and urine test, nitrogen balance assessment, and energy expenditure testing by indirect calorimetry will be performed at the beginning of the nutrition regimen and at 24 h, 72 h and 5–7 days after initiation. The sample size for this trial is estimated to be 90 participants (about 30 participants in each group). The data analysis will be by intention to treat.

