### Study outcomes

The primary outcome of the study will be the variation of NB from baseline to the study ending and the incidence of hyperproteinemia or uremia causing the need to stop the study. Secondary outcomes include the variation of plasma protein levels (total proteins, albumin, prealbumin, transferrin, and RBP), expenditure energy measured by indirect calorimetry, and the incidence of gastrointestinal complications (abdominal distension, vomiting, diarrhea, and excessive gastric residue) and metabolic acidosis.

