### Statistical analysis

As there are no previous studies reporting expected standard deviations, we use the standardized difference of means for computing the optimal minimum number of patients to include in the trial. The calculation of the sample size was carried out with EPIDAT 3.1 software. Given a significance level of 5% (type I error), a power of 80% (complementary of the type II error), and a minimum detectable standardized difference of means of 0.9, we need 30 patients per group (Bonferroni correction included).

We will use an intention-to-treat approach. A descriptive analysis will be performed where quantitative variables will be described by their means and standard deviations or their medians and interquartile ranges, as appropriate. The quantitative ones will be summarized by their absolute and relative frequencies. Parametric and non-parametric tests will be employed for contrasting equality among groups.

Univariate and multivariate mixed models will be used in order to assess the effects size of the different diets (fixed effects) on the patients (random effects) unadjusted and adjusted by potential confounders, respectively. *P* values under 5% will be considered statistically significant.

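### The sample size includes a Bonferroni correction that the 5% analysis threshold does not apply, and two primary outcomes have no stated error allocation

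*Protocol article*

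**What the plan says.** All of this is in the protocol article.

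- **Planning (Statistical analysis, first paragraph).** Type I error is 5%, power is 80%, and the target is a "minimum detectable standardized difference of means of 0.9". The result is "we need 30 patients per group (Bonferroni correction included". The number of comparisons behind the correction is not given.
- **Decision rule (same section, last paragraph).** P "values under 5% will be considered statistically significant". Neither adjusted P values nor a reduced level is mentioned.
- **Tests (same section).** Parametric or non-parametric tests of equality across the groups are planned, then mixed models with diet as a fixed effect. Individual contrasts are not listed.
- **Primary outcome (Study outcomes).** The change in NB to study end, "and the incidence of hyperproteinemia or uremia causing the need to stop the study". Both stand under one primary label, with no order, no split of the 5%, and no rule that both must succeed.
- **Aims.** The first hypothesis compares higher-protein feeding with the standard diet. The abstract's Background treats side effects differently from Study outcomes: "A secondary objective is to register possible secondary effects of the protein-enriched diet".
- **Arms (abstract, Methods).** Infants are "randomly allocated to one of three enteral feeding formulae with different protein contents".

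**The concern.** A Bonferroni correction works only if the reduced level is also used to judge the results. Here the correction raises the number of infants, but the sentence that decides which results count as significant does not carry it over. Read literally, a contrast with P = 0.03 would be called significant although the trial was sized on the basis that it would not be.

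The second primary outcome adds to this, because no rule says how the 5% is shared between efficacy and the stopping incidence. The Discussion expects the results to show how much protein can be recommended. That conclusion depends on comparing diets with each other, so the primary comparisons are where an unadjusted threshold would do harm.

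**Working it through.** **Inputs.** From Statistical analysis: α = 0.05, power 80%, standardized difference d = 0.9, n = 30 per group. From the abstract: three arms. From Study outcomes: two primary outcomes. Assumed because not stated: two-sided tests, no dropout, and a Bonferroni divisor k of 1, 2, 3 or 6.

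**Step 1: reproduce the 30 per group.** The normal formula is n = 2(z₁₋α/₂ₖ + z₀.₈₀)² / d², with z₀.₈₀ = 0.842 and d² = 0.81. The t-based values use the noncentral t distribution.

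| k | level | z | n, normal | n, t | power at 30 (normal / t) |
|---|---|---|---|---|---|
| 1 | 0.05 | 1.960 | 19.4 → 20 | 21 | 93.6% / 92.9% |
| 2 | 0.025 | 2.241 | 23.5 → 24 | 25 | 89.3% / 87.9% |
| 3 | 0.0167 | 2.394 | 25.8 → 26 | 28 | 86.3% / 84.3% |
| 6 | 0.0083 | 2.638 | 29.9 → 30 | 32 | 80.2% / 77.1% |

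For k = 3: 2 × (2.394 + 0.842)² / 0.81 = 25.8. An unadjusted 5% falls well short of 30, and so does k = 2. The planned figure fits k = 3 rounded up (28 by t) or k = 6 exactly (30 by the normal formula). The correction is therefore in the number, but its divisor cannot be recovered from the text.

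**Step 2: family-wise error for NB if each contrast is judged at an unadjusted 5%.** All three diets are taken as equal, with 30 per arm and 87 degrees of freedom.

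- Three pairwise contrasts: P(Q > 1.988 × √2) for the studentized range with three groups = 12.1%.
- Two contrasts against standard diet: 9.0%, from 400,000 simulated trials.
- Contrasts made only after a significant overall three-arm test: 5.0% in the same simulation.

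**Step 3: two primary outcomes.** With one overall test at 5% for each, the chance of at least one false positive is 1 − 0.95² = 9.75% if they are independent, and it cannot exceed 5% + 5% = 10%. The second outcome is binary and its event rate is not given. An exact test on sparse events uses less than its nominal 5%, so the true figure may be lower.

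**Step 4: the same design judged at the planned level.** For three pairwise NB contrasts at 0.05/3 = 0.0167, the critical t is 2.441. The studentized range then gives P(Q > 2.441 × √2) = 4.4%. Power for d = 0.9 at 30 per group is 84.3% by t.

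**The case against.** The strongest reply is that the text is ambiguous rather than contradictory. The section names Bonferroni, adjusted P values are commonly compared with 5%, and a condensed article may leave the mechanics to a fuller document. If adjusted P values were meant, or if both primary outcomes had to succeed, the inflation would shrink or vanish. What stands of this is that the intention may be sound. But the article does state a threshold, and that threshold carries no adjustment. A later document that applied the correction would have to depart from this sentence or reinterpret it.

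Three stronger readings are tempting, and the documents do not support them.

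- **Six primary tests with a family-wise error of about 23% to 26%.** No section lists three pairwise contrasts, let alone six tests. Tests of equality across groups fit one overall comparison, and the first hypothesis fits two contrasts with standard diet. The 23% (26% if all six tests are taken as independent) also treats the stopping incidence as if each test used its full 5%. As an illustration, assume Fisher's exact test on three pairs with 30 per arm. The chance of any false positive on that outcome is then 0.4%, 2.5% or 5.8% at assumed event rates of 5%, 10% or 20%. Combined with 12.1% for NB, as independent, the totals are about 12.5%, 14.4% and 17.2%.
- **An underpowered trial.** The 77% power is the t-based value for an assumed divisor of 6. The normal formula gives 80.2%, and the protocol claims neither that divisor nor a t test.
- **NB must become the only primary outcome.** The mismatch between the aims and Study outcomes needs an answer. But the trial is registered and has been recruiting since December 2016, so removing a named primary outcome is a substantive decision, not a change of wording.

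**Conclusion.** The point holds in a limited form. The planning statement and the decision rule use different error levels. Followed as written, the decision rule does not keep the stated 5% type I error.

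- **Ungated, unadjusted NB contrasts:** about 9% (two contrasts) to 12% (three).
- **Contrasts gated by an overall test:** NB alone stays near 5%, but two primary outcomes at 5% each can reach about 10%. The exact figure depends on the unstated event rate of the stopping outcome.

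These figures assume two-sided tests, 30 evaluable infants per arm, no true differences, and 5% applied to unadjusted P values. The list of contrasts is inferred from the three arms and the first hypothesis. The sample size of 30 per group is not in error: it delivers at least the planned 80% power at 0.0167, and about 77% (t) to 80% (normal) at 0.0083.

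**What to change.** For the primary analysis, replace the 5% sentence with the Bonferroni level used in planning, and state the contrasts and the divisor.

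- If the family is the three pairwise NB contrasts, judge each at two-sided 0.0167, or compare Bonferroni-adjusted P values with 5%. At 30 evaluable per group this gives about 84% power for d = 0.9 and a family-wise error of about 4.4%.
- State whether the stopping incidence belongs to that family or is reported as safety with confidence intervals. If it belongs (three contrasts on two outcomes, divisor 6, level 0.0083), NB power at 30 per group is about 77% to 80%, and 32 per group would restore 80% by the t-based calculation.

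Aligning the level on NB needs no extra infants. The cost is that P values between the corrected level and 0.05 can no longer be claimed as significant. If the status of the stopping outcome changes, the protocol and the registry entry need to be amended to match. The decision should be recorded before the data are analysed, all the more because the trial is open-label.

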## Discussion

Current recommendations about protein prescription in critically ill children are not based on randomized controlled trial (RCT) results. Data regarding protein supplementation are lacking. Studies with small sample sizes and heterogeneous patient populations are the only source for this information. A minimum intake of protein of 1.5 g/kg per day for children admitted to the PICU [16] is the current recommendation of the ASPEN in their latest guidelines. This recommendation is supported by only a systematic review [17] and a cohort study [18].

The exact and safe amount of protein needed to avoid negative PB remains unclear. Higher protein intake has been associated with early achievement of positive NB [19–21], and higher protein delivery has been related to lower mortality and higher ventilator-free days in PICU patients [23, 24]. On the other hand, enriched protein diets have been associated with elevated serum urea nitrogen levels [19, 20, 25, 26].

This RCT is designed to obtain new data about the amount of protein needed to avoid negative PB and the amount of protein that is safe without producing secondary effects. The results of the study will be important to decide whether a protein-enriched diet will or will not be useful in critically ill infants. Moreover, the results will be clinically significant to know the exact amount of protein we can recommend for critically ill infants.

In clinical practice, there is no method that can directly evaluate the protein metabolism. On the other hand, NB and serum protein levels have been used in most previous studies to estimate an adequate protein intake. We will use NB, considering a positive NB as an indicator of protein anabolism and a negative NB as protein catabolism. Moreover, we will evaluate as an indirect indicator of a protein metabolism improvement the increase of total proteins, albumin, prealbumin, RBP, and transferrin serum levels from baseline to the study endpoint.

The main problems we will face during data collection are the possible development, in any of the groups, of side effects that recommend to stop the study and the difficulty of including enough valid patients due to problems with urine collection.

In summary, this multicenter, prospective RCT will compare the effect of three different enriched-protein diets on serum levels of proteins, nitrogen balance, and energy expenditure in critically ill infants as well as their possible secondary effects.

## Trial status

The trial began recruitment at Hospital Gregorio Marañón on December 28, 2016. Participants will be recruited until December 2020 if necessary. During the period between approval of the protocol version (2010) and enrollment of the first patient (2016), no protocol amendments or enrollment attempts have occurred.

## Data Availability

The final datasets generated and analyzed in the current study will be available from the corresponding author on reasonable request and in ClinicalTrials.gov (NCT03901742).

## Abbreviations

ASPEN: American Society of Enteral and Parenteral Nutrition
NB: Nitrogen balance
PB: Protein balance
PICU: Pediatric intensive care unit
RBP: Retinol binding protein
RCT: Randomized controlled trial
SPIRIT: Standard Protocol Items: Recommendations for Interventional Trials
